## Abstract

**Background:**

Hydrogen gas inhalation (HI) improved survival and neurological outcomes in an animal model of post-cardiac arrest syndrome (PCAS). The feasibility and safety of HI for patients with PCAS was confirmed in a pilot study. The objective of this study is to evaluate the efficacy of HI for patients with PCAS.

**Methods/design:**

The efficacy of inhaled HYdrogen on neurological outcome following BRain Ischemia During post-cardiac arrest care (HYBRID II) trial is an investigator-initiated, randomized, double-blind, placebo-controlled trial designed to enroll 360 adult comatose (Glasgow Coma Scale score < 8) patients who will be resuscitated following an out-of-hospital cardiac arrest of a presumed cardiac cause. The patients will be randomized (1:1) to either the HI or control group. Patients in the HI group will inhale 2% hydrogen with 24% to 50% oxygen, and those in the control group will inhale 24% to 50% oxygen for 18 h after admission via mechanical ventilation. Multidisciplinary post-arrest care, including targeted temperature management (TTM) between 33 °C and 36 °C, will be provided in accordance with the latest guidelines. The primary outcome of interest is the 90-day neurological outcome, as evaluated using the Cerebral Performance Categories scale (CPC). The secondary outcomes of interest are the 90-day survival rate and other neurological outcomes. This study will provide 80% power to detect a 15% change in the proportion of patients with good neurological outcomes (CPCs of 1 and 2), from 50% to 65%, with an overall significance level of 0.05.

**Discussion:**

The first multicenter randomized trial is underway to confirm the efficacy of HI on neurological outcomes in comatose out-of-hospital cardiac arrest survivors. Our study has the potential to address HI as an appealing and innovative therapeutic strategy for PCAS in combination with TTM.

**Trials registration:**

University Hospital Medical Information Network (UMIN), 000019820. Registered on 17 November 2015.

**Electronic supplementary material:**

The online version of this article (doi:10.1186/s13063-017-2246-3) contains supplementary material, which is available to authorized users.

## Background

Anoxic neurological injury is a significant source of morbidity and mortality in cardiac arrest (CA) survivors [1]. Currently, targeted temperature management (TTM) is the only treatment that has both laboratory and clinical supportive data and is used to improve outcomes in patients with post-cardiac arrest syndrome (PCAS) [2, 3]. Although the optimum protocol for TTM has yet to be established, maintaining the body temperature between 32 °C and 36 °C, rather than not treating the fever, is now implemented as the gold standard for improving outcomes in patients with PCAS [4, 5]. Several drugs that block toxic metabolite production have shown promise in mitigating anoxic neurological injuries in animal PCAS models. However, these drugs have not been demonstrated to improve outcomes in clinical trials [6, 7]. Thus, a medical breakthrough is warranted in post-CA care, and we are in pursuit of a novel and simple therapeutic approach.

The unique antioxidative and antiapoptotic properties, as well as the potential therapeutic applications, of molecular hydrogen (H_2_) were first reported in 2007 [8]. Since then, the efficacy of H_2_ has been extensively studied in various animal models and preliminary clinical studies. In addition to its radical-scavenging effect, H_2_ has been reported to regulate gene expression and various signal transduction pathways by modifying the free radical chain reaction-dependent generation of oxidized phospholipid mediators [9]. Although the specific mechanisms underlying the pleiotropic effects demonstrated by H_2_ in various animal models have not been fully elucidated, the clinical translation of H_2_ is now attracting positive attention [10]. Improved survival rates, better neurological outcomes, and attenuated histological damage have been reported with hydrogen gas inhalation (HI) in a PCAS rat model. The salutary effect of H_2_ was comparable to that of TTM [11, 12]. With the unique features of H_2_, specifically its pleiotropic effects, high permeability, convenient administration, and lack of obvious adverse effects, HI has the potential to improve survival and neurological outcomes in patients with PCAS. Recently, we reported that HI is a feasible and safe approach for selected comatose post-CA patients [13]. Therefore, in this trial, we will evaluate whether HI is effective, compared with conventional oxygen inhalation, in improving 90-day neurological outcomes in comatose patients resuscitated after out-of-hospital cardiac arrest (OHCA) of a presumed cardiac cause.

## Methods/design

### Study design

The Efficacy of inhaled HYdrogen on neurological outcome following BRain Ischemia During post-cardiac arrest care (HYBRID II) trial is an investigator-initiated, randomized, placebo-controlled, double-blind multicenter superiority trial (RCT) with two parallel groups. Patients will be allocated 1:1 to either the intervention group or the control group. This RCT will be conducted at approximately 15 institutions in Japan. The goal of this trial is to evaluate the efficacy of HI on neurological outcomes in comatose patients who are resuscitated following OHCA of a presumed cardiac cause. This trial is registered with the University Hospital Medical Information Network (UMIN) clinical trials registry (UMIN000019820). A completed Standard Protocol items: Recommendations for Interventional Trials (SPIRIT) Checklist is available in Additional file 1.

### Inclusion criteria

The inclusion criteria are as follows: patients aged between 20 and 80 years; OHCA of a presumed cardiac cause with return of spontaneous circulation (ROSC) in a prehospital setting or in the emergency room (ER); unconscious (Glasgow Coma Scale [GCS] score < 8) after ROSC; systolic blood pressure (≥80 mmHg) with or without fluid loading, vasopressors, and/or inotropes; written informed consent obtained from the patient’s next of kin; and < 6 h lapsed after ROSC before HI initiation.

### Exclusion criteria

The exclusion criteria are as follows: known prearrest Cerebral Performance Categories scale (CPC) 3 or 4, known limitations in therapy and “do not resuscitate” order, association with trauma, intracranial bleeding, acute stroke, acute aortic dissection, malignancy in terminal stage, pregnancy, acute intoxication, oxygen (O_2_) saturation < 94% with 50% O_2_ inhalation and adequate positive end-expiratory pressure (PEEP), cardiopulmonary bypass use, and determined to be inappropriate for the study by the study investigators.

### Enrollment and withdrawal

The study participants are unconscious and hence are unable to provide consent themselves. Therefore, before a subject’s participation in the trial and after a full explanation of the study’s purpose and procedures, written informed consent will be obtained by site investigators from the patient’s next of kin present at the hospital. The participants will be asked whether they wish to continue participating in the study after they regain competent consciousness. The patient will be withdrawn from the study if the patient or the patient’s next of kin withdraws consent. All data obtained from that patient will be discarded. Patients will be enrolled by investigators at each hospital.

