### Outcome measures

The primary outcome is the proportion of participants achieving a favorable 90-day neurological outcome as defined by CPCs of 1 and 2 [14]. Secondary outcomes include the 90-day survival rate, survival time, GCS score, modified Rankin Scale (mRS) score, and Mini Mental State Examination (MMSE) results. Cognitive impairment among OHCA survivors is well known, and MMSE is the most commonly used instrument for brief cognitive function screening [15, 16]. We will also collect GCS scores for supplementary evaluation of the prevalence of disturbance of consciousness.

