### Sample size estimation

On the basis of published data [17], we expect the rate of favorable outcome achieved with the current comprehensive critical care, including TTM, in this population to be 50%. Because there are limited clinical data [13], we considered animal data [12] and assumed that the absolute risk reduction by HI is 15%; that is, the favorable neurological outcome rate improves from 50% to 65% with HI. A sample size of 167 patients in each group will provide 80% power to detect a 15% change in the proportion of good neurological outcomes (CPCs of 1 and 2), from 50% to 65%, with an overall significance level of 0.05 according to a two-sided χ^2^ test. A low rate of failure to follow-up is anticipated because of the short duration of the follow-up and the consideration of recent experiences in our previous study. Including an assumed incomplete patient data rate of 5%, 180 patients are required for each group, for a total sample size of 360.

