### Statistical methods

All statistical analyses, including the interim analysis, will be thoroughly performed by independent statisticians who are not involved in patient treatment or outcome assessment. Statisticians are blinded to the allocation code. Statisticians will perform statistical analyses according to predetermined data handling and statistical methods, and there will be no arbitrary interference. All analyses will be performed on a full-analysis basis. Baseline characteristics by group will be compared using descriptive analyses. The proportion of patients achieving good neurological outcomes at the end of the follow-up will be compared using the Pearson χ^2^ test, which will be the primary result of the trial. With regard to the secondary outcomes, the 90-day survival rate will be compared using the Pearson χ^2^ test; the duration of survival will be analyzed using Cox regression analysis; and other neurological outcomes, such as mRS, GCS, and MMSE scores, will be compared using the Mann-Whitney *U* test. All tests will be two-tailed, and a *P* value of 0.05 will be considered statistically significant. All data analyses will be performed using SAS version 9.3 software (SAS Institute, Cary, NC, USA).

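### Discarding all data on withdrawal of consent, when only patients who regain competence are asked for their own consent, makes patient-initiated deletions depend on outcome

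*Protocol article*

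**What the plan says.** Three rules in the Protocol article, Enrollment and withdrawal, work together. Entry is on written consent from the next of kin. Later, "The participants will be asked whether they wish to continue participating in the study after they regain competent consciousness". On withdrawal, "The patient will be withdrawn from the study if the patient or the patient’s next of kin withdraws consent", and then "All data obtained from that patient will be discarded". No exception is made for data already collected, for adverse events, or for 90-day CPC and vital status.

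The endpoint (Outcome measures): "The primary outcome is the proportion of participants achieving a favorable 90-day neurological outcome as defined by CPCs of 1 and 2".

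The analysis set (Statistical methods): "All analyses will be performed on a full-analysis basis". The article does not define it further.

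Sample size estimation adds 5% for incomplete patient data, reaching 180 per group. Interim analysis compares 90-day deaths only, after the first 100 patients have completed follow-up, with a stopping threshold of 0.9875 for the posterior probability that mortality is higher on hydrogen.

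**The concern.** The patient's own decision is sought after randomization, usually after the 18 h of gas, and only from those who have recovered enough to decide. Patients who die or stay unconscious are never asked. Regaining competence is not identical to CPC 1 or 2, but it lies close to it. Exclusion at that step is therefore conditioned on something near the primary outcome.

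This is an explicit instruction, so it cannot be treated as a detail left to an analysis plan. An analysis plan could not restore data that the protocol orders to be discarded. The stake is understated favourable-outcome rates in both arms, a treatment comparison whose validity rests on equal refusal by arm, and a mortality interim analysis run on a set from which survivors or deaths may have been removed.

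**Working it through.** **1. The plan's own figure.** Inputs from Sample size estimation: the assumed effect is that "the favorable neurological outcome rate improves from 50% to 65% with HI"; the χ² test is two-sided at 0.05; the stated size and power are given as "A sample size of 167 patients in each group will provide 80% power to detect a 15% change". With unpooled variance,

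n = (1.960 + 0.842)² × (0.50×0.50 + 0.65×0.35) / 0.15² = 166.6, so 167 per group.

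The stated 167 is reproduced. The pooled-variance formula gives 170. Dividing by 0.95 gives 176 or 179, against 180 stated. The sample size is not in question.

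**2. Model for the deletion.** Let p be the true favourable rate and w the share of favourable-outcome patients who refuse and are deleted. The documents give no value for w, so every w below is an assumption. With n = 180 per arm and no other loss:

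- apparent rate p′ = p(1 − w) / (1 − pw)
- patients left n′ = n(1 − pw)
- apparent odds = (1 − w) × p / (1 − p)

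The factor (1 − w) cancels from the odds ratio when w is the same in both arms.

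**3. Same refusal in both arms.** For w = 5%:

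- control: 0.475 / 0.975 = 48.7%
- hydrogen: 0.6175 / 0.9675 = 63.8%

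Power is for the Pearson χ² test, Φ[(δ − 1.96·SE₀)/SE₁], with pooled SE₀ and unpooled SE₁.

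| w | Deleted, control / hydrogen | Apparent rates | Difference (points) | Odds ratio | Power |
|---|---|---|---|---|---|
| 0% | 0 / 0 | 50.0% / 65.0% | 15.0 | 1.857 | 82.4% |
| 5% | 4.5 / 5.9 | 48.7% / 63.8% | 15.1 | 1.857 | 81.5% |
| 10% | 9.0 / 11.7 | 47.4% / 62.6% | 15.2 | 1.857 | 80.6% |
| 20% | 18.0 / 23.4 | 44.4% / 59.8% | 15.3 | 1.857 | 78.4% |

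If the full 5% allowance is used up first (171 per arm), w = 5% moves power from 80.4% to 79.5%. With both true rates at 50% and equal w, the rejection rate stays at 5.0%.

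**4. Different refusal by arm, no true effect (both 50%, 180 per arm).**

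| w hydrogen / control | Apparent difference (points) | Two-sided rejection rate |
|---|---|---|
| 5% / 5% | 0.0 | 5.0% |
| 10% / 5% | 47.37 − 48.72 = −1.35 | 5.7% |
| 15% / 5% | −2.8 | 8.1% |
| 20% / 10% | −2.9 | 8.3% |

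**5. Proxy withdrawals.** If a share u of patients with unfavourable outcomes is also deleted, the apparent odds become p(1 − w) / [(1 − p)(1 − u)]. The two kinds of deletion partly offset each other in the rates. The odds ratio is kept if (1 − w)/(1 − u) is the same in both arms.

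**6. Interim analysis.** With D deaths among n patients in an arm, the β(1,1) prior gives posterior mean (1 + D)/(2 + n). Deleting k survivors changes it to (1 + D)/(2 + n − k), which is higher. Deleting j patients who died changes it to (1 + D − j)/(2 + n − j), which is lower. The effect on the 0.9875 criterion cannot be sized, because the documents give neither a mortality rate nor a withdrawal rate.

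**7. What bounds would show.** For w = 5% in both arms, counting all deleted patients as favourable restores 50% and 65%. Counting them all as unfavourable gives 85.5/180 = 47.5% and 111.15/180 = 61.75%. A count by arm is enough to compute such bounds.

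**The case against.** The strongest reply is that the trial is double-blind, with covered cylinders and a secret allocation table, and that patients are sedated and paralysed while the gas is given. Equal refusal among recovered patients is then the natural expectation, and equal refusal leaves the odds ratio and type I error alone. At 5% refusal, 4.5 and 5.9 patients are lost per arm, fewer than the 9 (5% of 180) already allowed for. This stands, and it limits the size of the point. It does not remove it: the allowance replaces numbers but does not correct for losing mainly one outcome category, and blinding does not guarantee equal refusal if patients recover at different times or in different states.

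The Discussion's remark that refusals should not cause selection bias comes in its treatment of proxy consent and the delay before enrolment. It does not address later withdrawal by patients who have woken.

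Several stronger readings are tempting but not supported:

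- *The rule contradicts the full-analysis statement.* That set is undefined in the article, and its definition may sit in a document not shown. The two statements are unreconciled, no more.
- *The comparison is biased because more hydrogen patients recover.* Step 3 shows that more recoveries at the same refusal rate leave the primary comparison intact.
- *Power collapses.* An assumed 2% on control and 10% on hydrogen, with 171 per arm, gives an apparent 13.1 points and 67% power. Nothing in a blinded trial's documents supports a fivefold difference.
- *Deletions fall almost only on favourable outcomes.* Next of kin of unrecovered patients can withdraw too, so the mix is unknown.
- *No sensitivity analysis could help.* Cylinders are numbered 1 to 360 and tied to an allocation table, so the arm of a deleted patient is traceable in principle and bounds are possible.

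Finally, an ethics or regulatory condition may require deletion. The article does not say.

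**Conclusion.** The point holds in a limited form. The deletion rule removes randomized patients, and where the patient makes the decision it does so conditionally on a near-proxy of CPC 1 or 2. The certain consequence, if any recovered patients refuse and few next of kin withdraw, is understated favourable-outcome rates: about 1.3 points in control and 1.2 in hydrogen at an assumed 5% refusal in both arms, with about 1 point of power lost. The primary comparison is then sound. With patient-initiated deletions alone, it is biased only if refusal among recovered patients differs by arm. An assumed 10% against 5% under no true effect gives about −1.35 points and a rejection rate of 5.7%. The interim mortality comparison can shift either way, by an amount that cannot be computed from the article.

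All sizes rest on assumed refusal rates. The rule should be fixed, because it makes the trial depend on an equality that it leaves no stated means to check. It is not a flaw that invalidates the design or the sample size.

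**What to change.** Replace the discard sentence in Enrollment and withdrawal with these provisions:

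- Withdrawal stops further study procedures, and data collected up to that point are kept.
- Permission to record 90-day CPC and vital status is asked for separately.
- Data are deleted only when the patient or next of kin explicitly asks, or where an ethics or regulatory condition requires it.
- A de-identified count by arm is kept of allocated patients whose data were deleted.
- The primary result is accompanied by a sensitivity analysis that sets these patients all to favourable and then all to unfavourable.

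Statistical methods should then say how deleted patients stand in relation to the full-analysis set.

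The cost is an amendment to the protocol and consent form, with ethics review. No patients or procedures are added. Trial status and time line reports 2 patients enrolled on 19 October 2017, so a change made then would have covered nearly the whole trial. If deletion turns out to be compulsory, the count by arm and the bounds should still be considered, as far as that condition allows.

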### Randomization, blinding, and allocation

Owing to the limitations in transporting large gas cylinders in a timely manner and storing them in limited spaces at facilities, pairwise transportation and randomization will be performed. Thus, cylinders will be sequentially numbered from 1 to 360, and each of the 180 pairs (e.g., 1 and 2, 3 and 4,…) will be transported simultaneously from a storage center to a facility upon request. One of each pair of gas cylinders will contain hydrogen gas, and the other will contain a control gas. Because two cylinders will be used per patient, each pairwise shipment will contain four cylinders. Which of the gas cylinders of each pair contains hydrogen or control gas will be determined by selecting a random binary number generated by the Bernoulli distribution (probability 0.5) using a computer, and this information will be entered into an allocation table. The allocation table will be kept secret by the assignment manager until the time of the key opening. Before a pair of gas cylinders is transported from a storage center, the gas cylinders will be covered by cylindrical covers so that the contents of the cylinders (hydrogen or control gas) cannot be recognized. Every set of two patients at each center will be randomly allocated 1:1 to the hydrogen and control groups while maintaining blindedness.

### Study intervention

The intervention is the inhalation of the blinded trial gas, which will be initiated upon admission to the intensive care unit (ICU) and will be continued for 18 h, along with TTM (Fig. 1). The H_2_ group will be ventilated with 2% H_2_ and titrated O_2_, whereas the control group will be ventilated with conventional titrated O_2_ through the gas inhalation system, as described below.

**Fig. 1 Fig1:**
[figure not shown]
Flow diagram of the study design. Patients will be randomly allocated 1:1 to the hydrogen group or the control group using content-blinded cylinders. Trial gas inhalation will be initiated after intensive care unit admission and continued for 18 h. Multidisciplinary treatments, including targeted temperature management, will be performed in all patients according to the latest International Liaison Committee on Resuscitation (ILCOR) guidelines. *CPC* Cerebral Performance Categories scale, *GCS* Glasgow Coma Scale, *PCAS* Post-cardiac arrest syndrome, *PEEP* Positive end-expiratory pressure, *ROSC* Return of spontaneous circulation, *SpO*
_*2*_ Peripheral oxygen saturation

### Gas inhalation system

The inhalation of the trial gas will be conducted using a previously described system [13]. The study gas will be supplied from a cylinder with constant flow and will be mixed with oxygen from the mechanical ventilator (SERVO-s®; MAQUET Critical Care AB, Solna, Sweden) at the inspiratory duct. The cylinder is filled with 4% H_2_ and 96% nitrogen for the HI group and with 100% nitrogen for the control group (Fig. 2). Thus, the maximum O_2_ concentration is limited to 50% with our current HI system because prefilled 4% H_2_ in N_2_ is mixed with oxygen to obtain 2% H_2_ containing O_2_. The optimum combination values of tidal volume, respiratory rate, fraction of inspired oxygen, and trial gas flow rate, which are common for both groups, have been predetermined to obtain the above-mentioned gas composition. In our HI system, there is a discrepancy in both volume and composition between the gas emitted from the ventilator and the gas inhaled by the patient. To overcome this phenomenon, we need to deactivate the alarm on the ventilator, which works as a fail-safe under ordinary circumstances. Alternatively, we will install extra devices to monitor the tidal volume and O_2_ concentration throughout the intervention to ensure safety.

**Fig. 2 Fig2:**
[figure not shown]
System of trial gas inhalation. The trial gas will be inhaled through this system. Trial gas will be supplied from a cylinder with constant flow, and it will be mixed with oxygen from the mechanical ventilator (SERVO-s®; MAQUET Critical Care AB) at the inspiratory duct. The cylinder is filled with 4% H_2_ and 96% nitrogen for the hydrogen group and 100% nitrogen for the control group. A tidal volume and fraction of inspired oxygen meter will be used during trial gas inhalation to monitor ventilation

